##### Frequency and duration of cold hands sensation episodes

The subjects will record the frequency and duration of each episode of cold hands sensation. The average frequency and duration of attacks will be calculated weekly by dividing the total number of attacks and their duration by the number of a given weekly interval (observation period). The frequency and duration cold hands sensation episodes will be measured at baseline and at one, three, and five weeks thereafter. We will record the frequency and duration of cold hands sensation episodes by patient diaries.

##### Heart rate variation

The pathogenesis of cold hands sensation is still unclear. Neural and intravascular mechanisms are thought to be involved in the pathological progress. The role of the autonomic nervous system is most often discussed, with particular attention to sympathetic over-reactivity. HRV analysis is a reliable non-invasive test that is used assess autonomic nervous system function [23].

HRV will be measured using a Medicore SA-2000E analyzer (Medicore Co., Ltd., Seoul, South Korea) with four limb electrodes. To minimize the influence of confounding factors, all subjects were prohibited from using drugs, caffeine, tobacco, and alcohol for eight hours before HRV testing. The frequency domain methods of HRV analysis will be used. Low frequency (LF), high frequency (HF), LF:HF ratio, LF in normalized units, and HF in normalized units will be measured. LF reflects the sympathetic influence, whereas HF reflects the parasympathetic influence. The LF:HF ratio reflects the interaction between sympathetic and vagal activity. LF in normalized units and HF in normalized units are the respective values of LF and HF divided by the sum of LF plus HF and multiplied by 100; thus, the sum of LF in normalized units and HF in normalized units is 100 [24]. HRV measurements will be conducted at baseline and at one, three, and five weeks thereafter.

### Safety

The safety of this trial will be determined by red blood cell (RBC) count, hemoglobin level, platelet count, mean corpuscular volume (MCV), mean corpuscular hemoglobin (MCH) level, mean corpuscular hemoglobin concentration (MCHC), hematocrit (Hct), total white blood cell (WBC) count, erythrocyte sedimentation rate (ESR), aspartate aminotransferase (AST), alanine aminotransferase (ALT), blood urea nitrogen (BUN), and creatinine level, serum sodium level, serum potassium level, and serum chloride level. All subjects are evaluated twice, first at the screening visit and once more after the termination of acupuncture treatments. To monitor the safety of the acupuncture treatment, we will monitor the occurrence of edema, hemorrhage, and pain as adverse events.

Any reported adverse events will be recorded throughout the study and vital signs will be monitored at each visit. The subjects will be asked to voluntarily report information about adverse events, and the researcher will confirm the occurrence of adverse events through methods such as a medical interview. Details about adverse events, such as the date of occurrence, degree of severity, causal relationship with the treatment, other treatments or medications that are suspected to cause the adverse event, and treatment of the adverse event will be recorded in detail.

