## Background

One of the normal physiological responses to cold temperatures or emotional stress is a reduction of the skin temperature to preserve body heat and maintain a normal body core temperature. Reactions characterized by excessive peripheral vasospasm may evoke clinical symptoms, and complaints of cold hands sensation are very common among the general population [1]. Cold hands sensation is defined as hands that become intolerably cold when exposed to normal temperature, in which most individuals feel no cold. There can be a confusion between cold hands sensation and Raynaud’s phenomenon (RP), as both have cold hands as a symptom. The signs of RP include cold and numb hands when exposed to cold temperatures, with subsequent pain and skin becoming blue in colour [2]. In a community-based survey of approximately 7,000 people, almost 12% responded that they had experienced unusual sensitivity to cold temperatures in their fingertips or toes [3, 4]. This may be due to a mild, early manifestation of Raynaud’s phenomenon (RP) or may be related to RP [1, 5], which is characterized by a reversible digital vasospasm provoked by cold temperatures and/or emotional stress [6]. A study by Choi *et al*. [7] found that in South Korea, 43% of patients with an abnormal cold sensation in the hands or feet had RP, and that primary RP represented 73% of cases of RP, and many family physicians prescribe medications for cold hands sensation based upon treatment recommendations for RP [8].

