### Inclusion criteria

Participants must meet the following criteria for inclusion in the study: cold hands sensation or RP, photoplethysmography showing decreased arterial pulse amplitude or abnormal ischemic pulse waveform such as biphasic or monophasic wave, aged between 20 and 75 years, VAS score of >3 for cold hands sensation, symptom duration of least one month, available for follow-up during the entire trial period, and provide written informed consent.

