### Statistical analysis

The statistical significance level will be set at 5%, and the data will be processed with the last observation carried forward method for the intention-to-treat analysis. Statistical analysis in this study will be performed using IBM SPSS Windows version 19.0 statistical software (IBM Co., Armonk, NY, USA) and will be based on the Korean Clinical Trial Statistics Guidelines.

The study will identify the comparative equivalence of demographic variables and clinical characteristics between the experimental and control groups by performing the two sample t-test or Mann-Whitney U test if normality test is satisfied or not for continuous data, chi-square test for categorical data.

A repeated measure two-factor analysis will be performed to identify differences in VAS, blood perfusion, frequency and duration of cold hands sensation attacks and HRV scores between the experimental and control group based on time (baseline, weeks one, three, and five). If the interaction between group and time is statistically significant, the point at which the pattern of results between the two groups changes will be checked using the contrast analysis. To compare groups and the incidence frequency of adverse events related to acupuncture and medication, the chi-square test will be used.

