## Discussion

Cold hands sensation is a common disorder within the Korean population. In Korea, many physicians believe the phenomenon is related to RP, and they may prescribe pharmaceutical treatments similar to those used for patients with RP [5, 8]. However, there is no established guideline for RP therapy, and many of the agents most frequently used in the treatment of RP are used off-label [15] and consist mainly of vasodilators, in particular calcium channel antagonists such as nifedipine. While these agents have proven useful in some reports [14], in about 50% of patients, there is no beneficial effect [15]. Furthermore, their use has often been associated with an unacceptably high incidence of side effects including edema, flushing, erythema, dizziness, nausea, palpitations, and drowsiness [25, 26]. Beraprost is the first oral prostaglandin analog with vasodilatory and antiplatelet effects which has been used in the treatment of RP. To date, one double blind study has indicated that there was no difference between oral beraprost and placebo in the treatment of primary RP, and the same study found that patients in the beraprost group reported a significantly higher incidence of side effects including headache; dose increase was also limited by side effects such as headache, flushing, and diarrhea [15, 27]. The high prevalence of RP in the general population and the unfavorable side effects profiles of the present medications further demonstrate the need for alternative treatment options.

Acupuncture is one of the most important components of complementary and alternative medicine. It is a therapy that has been used for thousands of years in Korea. Recently, there has been increased interest in the therapeutic benefits of acupuncture [28]. In South Korea, many subjects with cold hands sensation already choose traditional Korean medicines such as acupuncture for treatment. However, thus far, there are no published controlled clinical trials investigating the efficacy and safety of acupuncture for treatment of cold hands sensation. We have therefore designed this pilot RCT to guide the design of a full-scale trial. Our study will be a first randomized controlled trial regarding cold hands sensation, but it has limitation of small sample size. We expect this pilot study to provide a clinical foundation for a future large-scale trial as well as information about the feasibility of such a trial.

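### Edema, hemorrhage and pain are not specific to acupuncture, so the between-group safety comparison should count them by randomised arm whatever their cause, not by judged cause

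*Protocol article*

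**What the plan says.** The Safety section names three events for the experimental treatment: "To monitor the safety of the acupuncture treatment, we will monitor the occurrence of edema, hemorrhage, and pain as adverse events". It adds that all reported adverse events are recorded throughout the study, and that each record includes the date, severity, causal relationship with the treatment, and any other treatment or medication suspected as the cause. A researcher confirms by interview or similar means that an event occurred. The section does not say who judges cause or by what rule.

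The Statistical analysis section gives the comparison: "To compare groups and the incidence frequency of adverse events related to acupuncture and medication, the chi-square test will be used".

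Other sections bear on what can cause the three events:

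- **Edema.** Of vasodilators, in particular calcium channel antagonists such as nifedipine, the Discussion says that "their use has often been associated with an unacceptably high incidence of side effects including edema, flushing, erythema, dizziness, nausea, palpitations, and drowsiness".
- **Hemorrhage.** The Discussion also states: "Beraprost is the first oral prostaglandin analog with vasodilatory and antiplatelet effects which has been used in the treatment of RP".
- **Pain.** The Background says: "The signs of RP include cold and numb hands when exposed to cold temperatures, with subsequent pain and skin becoming blue in colour". The Inclusion criteria admit subjects with "cold hands sensation or RP".
- **Exposure.** Under Medications, nifedipine and beraprost are prescribed to every subject in both groups. Only the experimental group receives acupuncture.

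**The concern.** The Safety section treats the three events as a measure of acupuncture safety, yet the article itself points to other sources for them. If events are sorted by judged cause before the arms are compared, the result depends on that sorting. In the experimental arm an edema may be filed under acupuncture or under medication. In the control arm it can be filed only under medication or disease. The acupuncture-related count is therefore fixed at zero in one arm, and randomisation does not protect the comparison.

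Errors in sorting also move events between two columns of the same arm. A drug edema filed under acupuncture raises the acupuncture-related count and lowers the medication-related count, although both arms take the same drugs. A needle-related event filed under medication does the reverse. These counts are part of what the pilot passes on to the full-scale trial.

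**Working it through.** The article states no adverse-event rate and no power for safety, so there is no figure to reproduce. The check is partly textual and partly algebraic.

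**1. How firm is each alternative cause?**

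| Event | Other source in the article | Strength |
|---|---|---|
| Edema | Side effect of vasodilators such as nifedipine; all subjects take nifedipine | Explicit, both arms |
| Pain | Sign of RP | Explicit for RP; RP is eligible but not required |
| Hemorrhage | Beraprost is antiplatelet; all subjects take it | Inference; hemorrhage is not listed as its side effect |

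**2. What misattribution does.** For one event type, let

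- n = subjects per arm. The total is 14 (Participants); 7 per arm is an assumption, as no allocation ratio is given.
- b = proportion with a drug- or disease-caused event, equal in both arms (assumed).
- a = additional proportion with an acupuncture-caused event, experimental arm only (assumed).
- m = share of background events in the experimental arm that are filed as acupuncture-related.
- r = share of acupuncture-caused events that are filed as drug- or disease-related.

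Expected counts:

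| Column | Experimental | Control |
|---|---|---|
| Acupuncture-related | n[a(1 − r) + bm] | 0 |
| Drug- or disease-related | n[b(1 − m) + ar] | nb |
| Any cause | n(a + b) | nb |

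The error in the acupuncture-related count is n(bm − ar). The error in the other column is n(ar − bm), equal and opposite. They cancel in the any-cause row, where the expected difference is na whatever m and r are. If m = r = 0, there is no error.

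**3. Illustrations with n = 7.**

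- No acupuncture harm (a = 0), b = 0.3, m = 0.5: 7 × 0.3 × 0.5 = 1.05 events credited to acupuncture against 0. Drug- or disease-related events are 1.05 against 2.1.
- As above with m = 1: 2.1 against 0, and 0 against 2.1.
- Opposite direction, a = 0.3, b = 0.3, m = 0, r = 0.5: acupuncture-related events are recorded as 1.05 when the true number is 2.1. Drug- or disease-related events are 2.1 + 1.05 = 3.15 against 2.1.

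**4. Effect on the test.** With a = 0, two-sided 5%, all outcomes enumerated for 7 v 7. Against a control count of 0, the uncorrected chi-square test first reaches significance at 4 v 0 (p = 0.018; 3 v 0 gives 0.051), and Fisher's exact test at 5 v 0 (p = 0.021).

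| b | m | Expected, acupuncture-related | False positives by judged cause, chi-square / Fisher | False positives any cause, chi-square / Fisher |
|---|---|---|---|---|
| 0.3 | 0 | 0 v 0 | 0 / 0 | 3.8% / 0.7% |
| 0.3 | 0.5 | 1.05 v 0 | 1.2% / 0.1% | 3.8% / 0.7% |
| 0.3 | 1 | 2.1 v 0 | 12.6% / 2.9% | 3.8% / 0.7% |
| 0.5 | 0.5 | 1.75 v 0 | 7.1% / 1.3% | 5.7% / 1.3% |
| 0.5 | 1 | 3.5 v 0 | 50% / 22.7% | 5.7% / 1.3% |

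Except where misfiling is near complete and the event is common, the distortion shows in the counts and not in the p-value.

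**The case against.** The strongest reply is that the Safety section already provides for the problem. It records other treatments or medications suspected as the cause, so a drug edema can be attributed correctly, and it records all reported events with no limit to one arm. This stands in part. The field makes correct attribution possible, and the data for an any-cause comparison will exist. But no rule is given for telling a needle-related event from a drug- or disease-related one, and the Design section's blinding covers outcome assessments and statistical analyses without mention of the causality judgement.

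A second reply is that the analysis sentence may simply mean comparing adverse-event incidence between groups, with acupuncture and medication naming the trial treatments. That reading is possible, and under it no sorting by cause takes place. The sentence still speaks of related events, so a team following it could reasonably filter by cause first.

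Three stronger readings are tempting, and the article does not support them.

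- A reader might infer that each of the three events has a named alternative cause present in both arms. That holds only for edema. Bleeding is inferred, and nothing ensures that RP is present in both arms of a 14-subject trial.
- A reader might infer that drug and disease events will be credited to acupuncture and so overstate its harm. They can be, but the error may also run the other way and hide needle-related harm.
- A reader might put a size on the bias, such as 10 to 30 percentage points for edema. Such a figure only restates an assumed event rate of 10% to 30% with complete misfiling.

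**Conclusion.** The point holds as a minor one. The three events do not isolate acupuncture, and a comparison by judged cause, which is the most natural reading of the Statistical analysis section, has a structural zero in the control arm and lacks the protection of randomisation. Misattribution can bias it in either direction.

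The size cannot be derived from the article. It depends on background rates and misfiling shares that are not given, and it is zero if attribution is always correct. The illustrations rest on an assumed 7 per arm and assumed rates. They suggest an error of about one or two events in one arm, seldom enough to change a test result. The any-cause comparison by arm is free of this error whatever the attribution. In a 14-subject pilot with no safety hypothesis, what is at stake is the accuracy of the reported counts.

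**What to change.** **Statistical analysis section.** Replace the adverse-event sentence with wording to this effect:

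> For each randomised arm we will report and compare the number of subjects with any adverse event, and with each of edema, hemorrhage and pain, whatever the cause, counting each subject once per event type. The judged causal relationship to acupuncture or medication will be reported descriptively only.

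**Safety section.** State that edema, hemorrhage and pain are monitored in the same way in both arms. The any-cause comparison is fair only if both arms are observed alike.

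**Cost.** Two sentences are reworded and no new data are needed, because all reported events and their judged cause are already to be recorded. Noting body site or timing relative to a session could help the descriptive account, but that is form-level detail and the fix does not depend on it. The small downside is that any-cause counts include some events unrelated to any treatment.

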### Withdrawal and dropout

All subjects will have the right to withdraw from the study at any time. Participation will be ended at any stage if the subject refuses to continue, withdraws consent, or violates the inclusion or exclusion criteria or the trial protocol. The trial will be stopped if the principal investigator believes that there are unacceptable risks of serious adverse events.

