## Methods/Design

### Design

The study is a randomized controlled pilot clinical trial. It is designed to obtain basic information of a further full-scale trial about acupuncture treatment in subjects with cold hands sensation. The protocols to be used adhere to the principles of the Declaration of Helsinki and have been approved by the Institutional Review Board of Daegu Catholic University Hospital (approval number IORG0004453), where the study will take place. The trial is registered with the Korean Clinical Research Information Service (CRIS) registry. Written informed consent will be obtained from each participant before any treatment is given.

The outcome assessments and statistical analyses will be performed by professionals blinded to the assignment of subjects. The trial process is presented in Figure 1. The trial will run for five weeks. Subjects will be randomly allocated to one of two groups, a control group, in which subjects will receive only medication for three weeks, and an experimental group, in which subjects will receive the same medication as well as nine acupuncture sessions (three sessions per week for three weeks). Assessments will be made at baseline and again at one, three, and five weeks thereafter. The five-week assessment will be performed two weeks after treatment cessation. This study will be conducted between late November 2013 to February 2014 which is winter season in South Korea. We will record room temperature to control for temperature bias in this clinical trial.

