### Participants

A target sample size of 14 subjects with cold hands sensation has been set. One of the main objectives of this study is to provide an estimate of the sample size required for the full-scale randomized controlled clinical trial.

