### Interventions

Subjects will be randomly divided into two treatment groups: an experimental group (acupuncture plus medication group) and a control group (medication only group). The medication will be administered every day for three weeks and the acupuncture sessions performed three times per a week for three weeks (nine times in total). There are no other interventions such as moxibustion, exercises, or lifestyle advice in this study.

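### Ending participation for any protocol or eligibility violation leaves the intention-to-treat analysis resting on carried-forward values, possibly more often in the acupuncture arm

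*Protocol article*

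**What the plan says.** Withdrawal and dropout: participation ends, at whatever stage, "if the subject refuses to continue, withdraws consent, or violates the inclusion or exclusion criteria or the trial protocol". Violations are not graded. Stopping study treatment is not separated from leaving the study, and nothing is said about measuring outcomes after removal. Refusal and withdrawal of consent stand in the same sentence; those are proper grounds for ending participation and are not at issue.

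Statistical analysis: "the data will be processed with the last observation carried forward method for the intention-to-treat analysis".

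Randomization: eligibility and consent are confirmed before allocation, so after that step the removal rule acts on randomised subjects.

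Design: "Assessments will be made at baseline and again at one, three, and five weeks thereafter".

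Interventions: both arms share the drug schedule ("The medication will be administered every day for three weeks"); only the experimental arm also has the sessions ("the acupuncture sessions performed three times per a week for three weeks (nine times in total").

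Participants: "A target sample size of 14 subjects with cold hands sensation has been set". The same section makes estimating the size of the full-scale trial a main objective.

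**The concern.** An ITT comparison needs the outcomes of all randomised subjects, whether or not they adhered. Here the plan stops collecting those outcomes when a subject deviates, then fills the resulting gaps with earlier values. The missing data are made by rule, and they could have been avoided in any subject still willing to attend.

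Read as written, the rule triggers easily. The duties in the protocol include daily medication, patient diaries, and eight hours without drugs, caffeine, tobacco or alcohol before each heart rate variability test. The experimental arm has nine acupuncture sessions on top of these. If a missed session counts as a violation, that arm has a route to removal that the control arm lacks, and loss would be linked to both adherence and allocation.

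At stake is the VAS difference at weeks 3 and 5. In so small a trial one or two removals can move it visibly, and the estimate is meant to inform the design of the next trial.

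**Working it through.** **Inputs from the protocol article.** Total 14 (Participants); 3 sessions per week for 3 weeks (Interventions); assessments at weeks 1, 3 and 5 after baseline (Design); LOCF (Statistical analysis).

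**Assumptions.** The allocation ratio is not stated, so 7 per arm is assumed. The article gives no VAS means and no violation rate, so those used below are illustrative.

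**1. The plan's own figure.** 3 x 3 = 9 sessions, as stated.

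**2. Weight of one removal.** 1/7 = 14% of an arm. Two removals after week 1 make 2/7 = 29% of that arm's week-3 and week-5 values carried forward.

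**3. Could the rule act unequally?** Suppose each contact is missed independently with probability p, and that one missed contact counts as a violation. The chance of at least one miss is 1 - (1 - p)^m. Control has m = 3 assessments. The acupuncture arm has m = 3 + 9 = 12 if sessions and assessments are separate visits. It has m = 10 if the week-1 and week-3 assessments fall on session days, as the columns of Table 1 allow; the excess is then seven visits.

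| p | Control (m = 3) | Acupuncture (m = 10 to 12) |
|---|---|---|
| 1% | 3.0% | 9.6% to 11.4% |
| 2% | 5.9% | 18.3% to 21.5% |
| 5% | 14.3% | 40.1% to 46.0% |
| 10% | 27.1% | 65.1% to 71.8% |

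Violations common to both arms (medication, diary, test preparation, eligibility) are left out. Including them would bring the arms closer together.

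**4. Effect on the week-3 difference.** Illustrative VAS means: acupuncture 5.5 at week 1 and 3 at week 3; control 4.5 at week 3. Two of 7 acupuncture subjects are removed after week 1, none in control.

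- LOCF mean in the acupuncture arm: (5 x 3 + 2 x 5.5)/7 = 26/7 = 3.71. Estimated difference: 4.5 - 3.71 = 0.79 cm.
- If the removed subjects would have reached the acupuncture mean of 3, the ITT difference is 4.5 - 3 = 1.5 cm. Understatement: 1.5 - 0.79 = 0.71 cm, which equals 2/7 x (5.5 - 3).
- If they would have reached only the control mean of 4.5, the acupuncture mean is (5 x 3 + 2 x 4.5)/7 = 24/7 = 3.43 and the ITT difference is 4.5 - 3.43 = 1.07 cm. Understatement: 1.07 - 0.79 = 0.29 cm (before rounding), which equals 2/7 x (5.5 - 4.5).

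**5. Removal before week 1.** Baseline is then carried forward and the removed subject's change is zero. If removed subjects would otherwise have had the arm's mean change, that change shrinks to 6/7 = 86% with one removal, 5/7 = 71% with two and 4/7 = 57% with three.

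**6. After the change.** If violators are still measured at weeks 1, 3 and 5, the rule itself forces no carried-forward values. LOCF is needed only after withdrawal of consent, refusal of follow-up or other loss.

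**The case against.** The strongest reply is that the two sections can be applied together. A reader might infer that the removal rule flatly contradicts ITT. It does not: the rule ends participation and takes nobody out of an analysis set, and LOCF keeps subjects with a recorded value in the analysis. This stands. The conflict is one of substance: what is lost is later observed data.

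A reader might also infer that the loss falls mainly on the acupuncture arm. The article does not support that. It gives no violation rate and does not say that a missed session is a violation. Both arms share medication, diary and test-preparation duties. Control subjects could also deviate by seeking acupuncture outside the trial, since Interventions allows nothing further and the Discussion says many such subjects already choose it. Only the weaker statement, possibly more often, survives.

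A third tempting reading is that a responder whose VAS falls to 3 or below breaches the entry threshold and is removed. This fails. Inclusion criteria sets conditions for entry, and Randomization has them confirmed before allocation.

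The size of the bias rests on invented means and a chosen 2-to-0 split, and it arises through LOCF. That is right, which is why a range is given and not the larger figure alone.

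Finally, a condensed article may leave the grading of violations and follow-up after withdrawal to the full protocol. That would excuse silence. Here a rule is stated, without qualification, and it is the stated rule that causes the problem.

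**Conclusion.** The point holds as a weakness of design. As written, a randomised subject who violates an eligibility criterion or the protocol leaves the trial, and outcome measurement ends too. The ITT analysis then uses LOCF values where outcomes could have been observed, possibly more often in the acupuncture arm.

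Assuming 7 per arm, each removal is 14% of an arm. In the illustrated case the week-3 difference is understated by about 0.3 to 0.7 cm. The lower end applies if the removed subjects would have done no better than control, the upper end if they would have done as well as the rest of their arm. Both ends depend on the assumed means and on two removals in one arm only. The direction depends on it too: in improving subjects, carrying old values forward in the control arm would overstate the difference instead. The article gives no figures from which an expected bias could be computed.

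**What to change.** In Withdrawal and dropout, separate leaving the study from deviating from it:

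- A protocol or eligibility violation found after randomisation is recorded as a deviation.
- The subject continues with the scheduled week-1, -3 and -5 assessments unless he or she withdraws consent or refuses further follow-up.
- The subject stays in the ITT set with observed values. A per-protocol analysis is supportive only.
- Decisions to stop treatment for clinical reasons are unchanged.

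Statistical analysis should then say that LOCF applies only where an outcome could not be obtained.

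The cost is a short change of text and at most three already scheduled assessments per affected subject. The sample size does not change. Trial status says that recruitment has finished. If follow-up is also complete, outcomes lost in this way cannot be recovered at analysis. The report should then give the number of subjects removed for violations, by arm, reason and last assessment, and the changed rule should go into the full-scale protocol.
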